#### Biochemical Assessment of Micronutrient Status

In order to validate the information related to dietary intake, every 5th woman enrolled in the intervention and control groups—a subset of 30 women from each group—will undergo a free biochemical assessment of serum iron, ferritin, calcium, and vitamin D at baseline and at the end of the study at the AKUH laboratory. The specimens will be discarded once analyzed by the laboratory.

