**Methods:**

A randomized controlled trial was initiated at the Aga Khan University Hospital in Karachi, Pakistan, in January 2020. We aim to recruit 300 pregnant women in their first trimester who have smartphones, do not have comorbidities, and are not taking medications. The intervention group will be trained to use an mHealth app called *PurUmeed Aaghaz*. Through this app, the subjects will report information about their diet, supplement use, and physical activity and will receive personalized advice and three push messages as weekly reminders. The research assistant will obtain similar information from the control group via a paperless questionnaire; this group will receive standard face-to-face counseling regarding diet, supplement use, and physical activity. Data will be collected at enrollment and during four follow-up sessions scheduled 6 weeks apart. Primary study outcomes include improvements in diet (ie, change in mean dietary risk score from baseline to each follow-up), supplement use (ie, changes in mean supplement use score and biochemical levels of folic acid, iron, calcium, and vitamin D on a study subset), and mean duration of reported physical activity (minutes). Secondary study outcomes relate to maternal health (ie, gestational diabetes mellitus, gestational hypertension, pre-eclampsia, and gestational weight gain), newborn health (ie, birth weight and length and gestational age at delivery), and infant health (ie, BMI and blood pressure at 1 year of age). Compliance will be determined by the proportion of participants who complete the 6-month coaching program. Usability will be assessed based on features related to design, interface, content, coaching, perception, and personal benefit.

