#### Supplement Use

WHO guidelines for micronutrient supplements during pregnancy will be used to counsel women. These will include daily oral supplements of folic acid (0.4 mg) [48], iron (30-60 mg) [49], calcium (1500-2000 mg) [49], and vitamin D (200 IU) [50].

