### Expected Primary Outcomes

#### Dietary Intake: Quantity and Quality

Change in dietary intake between baseline and four subsequent follow-up visits 6 weeks apart will be assessed through a questionnaire. Based on consumption recorded in the food diary, data will be collected on the frequency and amount of all kinds of food consumed at each meal, including fruits and vegetables, red meat, white meat, legumes, nuts, eggs, dairy products, added table salt, and drinks (eg, carbonated drinks, fresh juices, and prepared juices). Averages will be calculated to determine the daily intake. Food sizes and amounts will be explained with the help of model utensils (ie, plate, bowl, and glass).

Dietary risk scores, ranging from 0 to 18, will be calculated based on the consumption of food items from six main food groups. Based on portions and diet quality, the score for each food group will be 0, 1.5, or 3 (Table 1) [58]. The total score will be the sum of individual food group scores. The higher the aggregate score, the poorer the dietary quantity and quality, and vice versa. Hence, a score of 18 indicates a highly inadequate dietary intake, a score of 9 indicates a nearly adequate dietary intake, and a score of 0 indicates an adequate diet [58].

**Table 1 table1:** Dietary risk score for six food groups.

Food group and characteristics^a^		Dietary risk score		
		0	1.5	3

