**Measurement of outcomes**																						
	Diet: dietary risk score			X		X			X				X			X						
	Supplement use: biochemical assessment			X												X						
	Physical activity: change in duration			X		X			X				X			X						
	Maternal gestational diabetes					X			X				X			X						
	Maternal gestational hypertension					X			X				X			X						
	Maternal pre-eclampsia					X			X				X			X						
	Maternal weight gain			X					X							X						
	Newborn preterm birth																		X			
	Newborn birth weight and length																		X			
	Infant BMI and blood pressure																					X
	mHealth program compliance and usability															X						

^a^X indicates that the item took place or was measured at this time point.

^b^mHealth: mobile health.

^c^The mHealth coaching intervention occurs continuously over the study period and not just at the specific time points.

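### The blood markers are said to validate reported diet, but the same nutrients are counselled as daily tablets and the protocol elsewhere counts the same assays as a supplement-use outcome

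*Protocol article*

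**What the plan says.** Four parts of the protocol article bear on this.

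- **Biochemical Assessment of Micronutrient Status** gives the purpose, "In order to validate the information related to dietary intake, every 5th woman enrolled in the intervention and control groups", and describes "a subset of 30 women from each group" having a "biochemical assessment of serum iron, ferritin, calcium, and vitamin D at baseline and at the end of the study". Supplements are not mentioned there. Specimens are discarded once analysed.
- **Abstract, Methods** places the same measurements under supplement use, within the primary outcomes: "changes in mean supplement use score and biochemical levels of folic acid, iron, calcium, and vitamin D on a study subset". It also says that the control group receives face-to-face counselling that covers supplements.
- **Table 3, Measurement of outcomes** has the row "Supplement use: biochemical assessment", marked at baseline and at 24 weeks.
- **Counseling, Supplement Use** sets out the tablets: "These will include daily oral supplements of folic acid (0.4 mg) [48], iron (30-60 mg) [49], calcium (1500-2000 mg) [49], and vitamin D (200 IU)".

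The dietary outcome is described this way: "Dietary risk scores, ranging from 0 to 18, will be calculated based on the consumption of food items from six main food groups". Supplement use is recorded separately, as the frequency of each of the four supplements, and scored from 0 to 12.

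**The concern.** One set of blood results is given two readings: evidence that diet reports are true, and an effect of taking tablets. These conflict, because each assayed nutrient reaches the woman by both routes.

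The overlap is built into the intervention. The app gives advice and push messages on diet and supplements together. If it works, reported diet and tablet use improve together in the intervention group, and a marker that responds only to tablets would move in step with the diet reports. Someone following the stated purpose could then credit the diet questionnaire with validity that the assays had not shown.

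This matters because the diet and supplement reports are subjective, the trial is unblinded, and the Limitations section expects information bias. The assays are the only laboratory check described on those reports.

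**Working it through.** **1. Subset size.** 300 women allocated 1:1 gives 150 per group. Every fifth woman gives 150/5 = 30 per group, which matches the document.

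**2. Assays against tablets.**

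| Nutrient | Assayed in the substudy | Counselled as a daily tablet | Listed as a supplement-use biochemical outcome in the Abstract |
|---|---|---|---|
| Iron | yes (serum iron, ferritin) | yes | yes |
| Calcium | yes | yes | yes |
| Vitamin D | yes | yes | yes |
| Folic acid | no | yes | yes |

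No assayed nutrient is free of a counselled tablet, so none can serve as a diet-only marker. The folic acid row is a plain mismatch: an outcome is listed with no assay behind it, and discarded specimens cannot be re-assayed.

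**3. How large could false agreement be?** This is an illustration on assumed inputs, since the document gives none. Let a marker M depend on tablets S and not on diet, with tablets explaining a share b² of its variance. Let reported diet D correlate ρ with tablet use. Then corr(D, M) = b × ρ.

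| Share b² | ρ = 0 | ρ = 0.3 | ρ = 0.5 |
|---|---|---|---|
| 0.10 | 0 | 0.09 | 0.16 |
| 0.20 | 0 | 0.13 | 0.22 |
| 0.40 | 0 | 0.19 | 0.32 |

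For example, √0.40 × 0.5 = 0.32. The problem disappears only if diet reports and tablet use are unrelated, which is unlikely when one program coaches both.

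**4. Could the data tell this from real agreement?** The Results section reports 66 women lost, 42 of them in the intervention group, so 24 in the control group. If the same losses apply to the subset:

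- intervention: 30 × (1 − 42/150) = 21.6, about 22 pairs
- control: 30 × (1 − 24/150) = 25.2, about 25 pairs
- total: about 47 pairs

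The Fisher-z 95% interval around r = 0 is ± tanh(1.96/√(n − 3)). For n = 60 this is tanh(1.96/√57) = 0.25. For n = 47 it is tanh(1.96/√44) = 0.29. The false correlations in step 3 cover nearly the same range. A larger subset would narrow the interval but would not remove the mixing of sources.

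**5. Comparing arms.** The Abstract frames the outcome as change in biochemical levels, and the Statistical Analysis section offers t tests and Mann-Whitney U tests for continuous variables. That section does not name the markers, and its list of adjustment variables does not include the baseline marker level. With equal variance at both draws and correlation r between them, the variance of the arm difference is proportional to 2(1 − r) for raw change and to 1 − r² for the 24-week level adjusted for baseline. The ratio is (1 − r²)/[2(1 − r)] = (1 + r)/2, which is below 1 whenever r is below 1. Adjustment is therefore at least as precise, from data already collected.

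**The case against.** The strongest reply is that the Abstract and Table 3 already tie the assays to supplement use, so the substudy section is a loose sentence and not a flawed design. Much of that stands, and it is why the remedy is mainly a reconciliation. But the substudy section is where the assays are defined, and it gives diet as their only purpose.

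A second reply is that tablet frequency is recorded at each visit and can be used to stratify or adjust, perhaps in an analysis plan not shown. This also stands in part. A reader might infer that the validation cannot work at all, and the document does not support that. The recorded variable covers frequency only, however, and the substudy section does not link it to the validation.

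A third reply is that the diary collects amounts of each food, and scoring fat as a share of calories already needs some conversion from food to energy. Nutrient intake might therefore be estimated, and it would be wrong to say that none can be derived.

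Two other inferences are tempting. One is that serum iron and serum calcium do not track intake. The other is that plasma expansion lowers the markers in every woman by the second draw. Both rest on outside physiology, and nothing in the document addresses them. Any shift with gestation should also be similar in both randomised groups, since they share one visit schedule. It would mislead only if a within-group change were read as an effect.

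**Conclusion.** The concern holds in a limited form. The document assigns conflicting purposes to one set of assays, and lists folic acid as an outcome without assaying it. Used as the substudy section states, the markers could credit tablet effects to diet reports.

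The possible false correlation of 0.09 to 0.32 rests on assumed inputs (tablets explaining 10 to 40% of marker variance, and a correlation of 0.3 to 0.5 between reported diet and tablet use). It falls to zero if that correlation is zero. The figure of about 47 pairs assumes that the subset loses women at the same rate as its group.

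The point does not affect the randomised comparison of the diet, supplement or activity scores. It limits what the assays can be said to prove about the diet reports. The document gives no ground for discarding any of the four markers or reducing serum iron and calcium to descriptive use.

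**What to change.** 1. Amend the substudy section to agree with the Abstract and Table 3, stating that the markers support the supplement-use score.
2. If dietary validation is kept as a further aim, stratify or adjust it for the recorded frequency of the matching supplement, and say that the markers alone do not validate diet.
3. Reconcile the folic acid listing in the Abstract with the assays actually done.
4. Compare groups on the 24-week marker level adjusted for the baseline level. Add gestational age at the draw for precision, since enrolment can fall anywhere in the first trimester. Do not interpret within-group change as improvement.

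The cost is wording and a small regression model, with no new samples or assays. The trial gives up the claim that the markers validate diet reports on their own. Precision stays limited, at about 22 and 25 pairs under the loss assumption, and the report should say so. The change should be fixed before the data are analysed.

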#### Outcome Assessment Questionnaire

A brief questionnaire has been developed to record information about the study outcomes. The data about maternal and newborn outcomes will be obtained from the medical records, while infant height, weight, and blood pressure will be measured by the trained research assistant.

#### Usability Assessment Questionnaire

A questionnaire containing 26 questions has been developed to assess the experience of using the mHealth program based on six domains: design, interface, content, coaching, perception, and personal benefit (Figure 3) [36].

**Figure 3 figure3:**
[figure not shown]
Components of the usability assessment of the mobile health (mHealth) app.

### Sample Size Calculation

Sample size has been calculated using OpenEpi (version 3.01). Based on assumptions of an α error of .05, a β error of .2, a 1:1 ratio of exposed to intervention to unexposed to intervention, and improvement in dietary intake and supplement use by 30% in the intervention group from a baseline of 20% [36], a sample size of 45 women in each group will be required. Based on the hypothesized 20% improvement in physical activity from a baseline of 36% [57], our sample size requirement increased to 107 women in each group. To reach 65% compliance [36], approximately 300 women will be needed for this study.

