### Study Hypothesis

We hypothesize that the mHealth coaching program will be effective in improving diet and supplement use among pregnant women by 30% and physical activity by 20% during the study period.

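### The physical activity sample size compares two proportions (36% vs 56%), but the declared outcome is mean minutes, so the stated 80% power does not belong to that outcome

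*Protocol article*

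**What the plan says.** All references are to the protocol article.

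- **Sample Size Calculation.** The general assumptions are given as "Based on assumptions of an α error of .05, a β error of .2" with "a 1:1 ratio of exposed to intervention to unexposed to intervention". For diet and supplements the text reads "improvement in dietary intake and supplement use by 30% in the intervention group from a baseline of 20% [36], a sample size of 45 women" per group. For physical activity it reads "Based on the hypothesized 20% improvement in physical activity from a baseline of 36% [57], our sample size requirement increased to 107 women in each", that is, 107 per group. A 65% compliance step then leads to roughly 300 women.
- **Abstract, Methods.** The physical activity primary outcome is "mean duration of reported physical activity (minutes").
- **Expected Primary Outcomes, Physical Activity.** The questionnaire records intensity and minutes. Activities are sorted into mild, moderate and vigorous, and no adequacy cut-off is set.
- **Table 3, Measurement of outcomes.** The entry is "Physical activity: change in duration".
- **Study Hypothesis.** The program is expected to succeed in "improving diet and supplement use among pregnant women by 30% and physical activity by 20% during the study period". The text does not say whether these percentages are absolute or relative.
- **Statistical Analysis.** A mixed model is planned for the fraction of women who score adequately at each follow-up. Scores are defined for diet (Table 1) and supplements (Table 2) only.

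**The concern.** A baseline of 36% can enter a sample size formula only as a proportion of women. The outcome is a duration. These are different quantities with different effect measures. A shift of 20 percentage points in the share of women who are active does not fix a difference in mean minutes, and power for mean minutes depends on an SD that is not among the inputs.

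This matters because physical activity raises the requirement from 45 to 107 per group and so drives the size of the trial. A reader who sees 80% power beside a hypothesis of a 20% improvement may take it that the trial had an 80% chance of detecting 20% more minutes. Nothing in the article supports that, and a null result on minutes could be over-read on the strength of it.

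**Working it through.** **1. Reproduce the printed figure.** Inputs from Sample Size Calculation: α = 0.05 (taken as two-sided, which is not stated), power 0.80, 1:1 allocation, p1 = 0.36, p2 = 0.36 + 0.20 = 0.56.

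Uncorrected size per group, with p̄ = 0.46 and Δ = 0.20:

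n0 = [1.960·√(2·p̄·(1−p̄)) + 0.842·√(p1(1−p1) + p2(1−p2))]² / Δ² = 96.3

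With the continuity correction:

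n = (n0/4)·[1 + √(1 + 4/(n0·Δ))]² = 106.06, rounded up to **107**. This matches.

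The same formula for 20% vs 50% gives 44.9, rounded up to **45**, which matches the diet and supplement figure.

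Alternatives for physical activity that do not give 107:

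| Variant | n per group |
|---|---|
| 36% vs 56%, two-sided, no correction | 97 |
| 36% vs 56%, one-sided, corrected | 86 |
| 20% read as relative (36% vs 43.2%), two-sided, corrected | 751 |

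The sizing therefore uses proportions of women and a shift of 20 percentage points. The arithmetic is right.

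**2. What 107 per arm gives for a mean.** For an unadjusted two-sided t test at one visit (noncentral t), 80% power at 107 per arm needs a standardised difference of about **0.385 SD**. The normal approximation (1.960 + 0.842)·√(2/107) gives 0.383.

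**3. If the sized shift is real and minutes are roughly normal.** A move from 36% to 56% above a fixed cut-off equals z(0.56) − z(0.36) = 0.151 + 0.358 = 0.51 SD. Power for a comparison of means is then about **96%** at 107 per arm and 99% at 150 per arm.

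**4. If 20% is taken as a relative rise in mean minutes.** The standardised difference is 0.20/CV, where CV is the SD divided by the mean. The article gives no mean or SD, so the CVs are assumptions.

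| Assumed CV | Difference in SD | Power, 107 per arm | Power, 150 per arm |
|---|---|---|---|
| 0.5 | 0.40 | 83% | 93% |
| 0.6 | 0.33 | 68% | 82% |
| 0.8 | 0.25 | 44% | 58% |
| 1.0 | 0.20 | 31% | 41% |

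At 107 per arm, 80% is reached only if the CV is at most 0.20/0.385 ≈ 0.52.

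**5. Reading.** The same 107 per arm corresponds to anything from about 31% to about 96% power, depending on what the effect is taken to be and on a CV the article does not give.

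**The case against.** The strongest defence is that Statistical Analysis does plan a proportion analysis, the mixed model for the fraction scoring adequately, and that its list of t-test and chi-square comparisons does not name physical activity. On that view the sizing and the analysis agree. Part of this stands: a t test on mean minutes is inferred from the outcome definition and is not spelled out. But the link does not close. Scores and adequacy levels exist only for diet and supplements. The 150 minutes per week appears as guideline and counselling content, and nothing ties it to the 36%. A fuller document could define a cut-off, but the outcome named in this article would still be minutes.

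A reader might infer from step 4 that the trial is well short of 80% power. The article does not support that, for three reasons.

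- The low figures need 20% to be a relative rise in mean minutes, whereas the 107 reproduces only with percentage points. On the shift actually sized, step 3 gives about 96%.
- Every CV is assumed.
- The table uses one unadjusted visit, while the plan has repeated measurements. As an illustration, take a correlation of 0.5 between all visits and a baseline-adjusted mean of four follow-ups, with 108 and 126 women (150 per arm assumed, less the 42 and 24 losses implied by Results). Power for the same 20% rise is then about 99%, 87% and 70% at CV 0.6, 0.8 and 1.0. This too rests on assumption, but it shows how far the shortfall depends on the method.

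It can also be said that physical activity is singled out. Diet and supplements do show the same pattern, with 20% vs 50% in the sizing and mean scores as outcomes. That requirement is 45 per group and does not set the trial size.

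**Conclusion.** The mismatch is real. The calculation that drives the trial size is correct for 36% vs 56% of women, but the declared outcome is mean minutes, and no yes/no physical activity outcome or cut-off is defined. The printed 80% power is therefore not a property of the declared outcome. True power may be higher (about 96% at 107 per arm, assuming a real 36% to 56% shift and roughly normal minutes) or lower (68% at an assumed CV of 0.6 and 31% at 1.0, for a 20% relative rise tested at one visit without adjustment). Underpowering is not shown. What can be stated without a CV is that 107 per arm gives 80% power for about 0.385 SD, unadjusted. Recruitment is complete, so the remedy is a corrected statement and not a new sample size.

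**What to change.** Before analysis:

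1. Keep mean minutes as the physical activity primary outcome.
2. State that 107 per arm gives 80% power for a difference of about 0.385 SD (unadjusted, two-sided 0.05). Convert this to minutes with the pooled baseline SD, computed without regard to arm.
3. State that 20% in the sizing means 20 percentage points in the proportion of women, and is not a 20% rise in mean minutes. Note that the diet and supplement sizing likewise rests on proportions while the outcomes are mean scores.
4. The proportion reaching 150 minutes per week may be added only as a supportive analysis, labelled as added after recruitment. It should not replace the primary outcome: the trial is unblinded and Results reports that 170 women have completed all four follow-ups, so a swap now would be open to the charge of outcome switching.

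The cost is some rewording, one SD from data already collected, and possibly a less favourable power statement. No new data are needed.

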### Type of Analysis

The data for the study participants will be analyzed based on the group to which they were initially assigned, irrespective of the intervention they received using the intention-to-treat approach [71]. This will preserve the benefits of randomization and will allow us to draw inferences regarding the efficacy of the intervention [71].

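### The enrolment target of 300 does not follow from 107 per group at 65%: those inputs need 330 women, and 300 matches only a smaller per-group size that the plan does not state

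*Protocol article*

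**What the plan says.** All the inputs are in the protocol article, Sample Size Calculation. The error rates are "an α error of .05, a β error of .2", with 1:1 allocation and OpenEpi as the software. For diet and supplement use (a 30% improvement from a 20% baseline), "a sample size of 45 women in each group will be required". For physical activity (a 20% improvement from a 36% baseline), "our sample size requirement increased to 107 women in each group". The section then moves to the total: "To reach 65% compliance [36], approximately 300 women will be needed for this study". It does not show how 107 per group became 300, and it does not name the formula.

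Three other places bear on this:
- mHealth Outcomes defines compliance as the percentage of participants who complete the 6-month programme. The secondary objectives assess it in the intervention group.
- Type of Analysis keeps women in their assigned group "irrespective of the intervention they received using the intention-to-treat approach".
- Statistical Analysis plans chi-square tests for proportions, without mentioning a continuity correction, and multiple imputation for women who leave early.

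**The concern.** A reader takes the section to say that 300 women, with 65% of them counting, yield the 107 per group that 80% power requires. They do not. The total is 30 women (9%) below what the stated inputs give, and the word approximately does not stretch that far.

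This matters because physical activity is one of the three primary aims and the one that set the size. The paragraph is what readers will use to judge whether a null result is informative. As written, they cannot tell which per-group size, which formula or which allowance for loss the trial was built on.

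**Working it through.** **Inputs** (Sample Size Calculation): α = 0.05, β = 0.2, 1:1 allocation, 20% to 50% for diet and supplements, 36% to 56% for physical activity, 65% compliance, total about 300. Two choices are inferred because they reproduce the plan's figures: a two-sided test, and improvements read as absolute percentage points.

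**Step 1: reproduce the per-group sizes.** With d = p2 − p1 and p̄ the mean of p1 and p2:

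- Uncorrected: n = [1.960·√(2p̄(1−p̄)) + 0.842·√(p1(1−p1) + p2(1−p2))]² / d²
- Continuity-corrected: n_c = (n/4)·[1 + √(1 + 4/(n·d))]²

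| Comparison | Uncorrected n | Corrected n_c | Plan |
|---|---|---|---|
| 20% vs 50% | 38.5, so 39 | 44.9, so 45 | 45 |
| 36% vs 56% | 96.3, so 97 | 106.1, so 107 | 107 |

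For 36% vs 56%: p̄ = 0.46, the two square roots are 0.7048 and 0.6905, and d = 0.20. Both of the plan's figures match the corrected formula exactly, so the per-group sizes are sound and the fault is in the last step.

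**Step 2: inflate for 65%.**

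- 2 × 107 = 214, and 214/0.65 = 329.2. By group, 107/0.65 = 164.6, so 165 per group and 330 in total.
- In reverse, 300 × 0.65 = 195, or 97.5 per group.
- 300 keeps 214 women only if 214/300 = 71.3% are retained, which is a loss of 1 − 0.713 = 28.7%.

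**Step 3: look for a route to 300.**

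- Multiplying instead of dividing: 214 × 1.35 = 289. No match.
- Inflating the intervention arm only: 107 + 107/0.65 = 272. No match.
- Starting from the uncorrected size: 97/0.65 = 149.2, so 150 per group and 300 in total. This matches, but the plan states 107, not 97.

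**Step 4: power for 36% vs 56% at 97 per group.** Power = Φ{[δ − 1.960·√(2p̄(1−p̄)/n)] / √([p1(1−p1) + p2(1−p2)]/n)}. With n = 97 the two square roots are 0.0716 and 0.0701.

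- Uncorrected, δ = 0.20: Φ(0.852) = 80.3%.
- Corrected, δ = 0.20 − 1/97: Φ(0.705) = 76.0%.

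**Step 5: set against the loss reported so far** (Results). 66 of 300 women (22.0%) were lost, 42 of them in the intervention group. Taking 150 per arm (50 blocks of 6 at 1:1), 150 − 42 = 108 and 150 − 24 = 126 remain. Both exceed 107, the intervention arm by one woman. Only 170 of the remaining 234 had completed all four follow-up sessions.

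**The case against.** The strongest reply is that 300 is adequate for the test actually planned. The protocol names chi-square tests and no continuity correction. The uncorrected requirement is 97 per group, and 300 at 65% supplies it with 80.3% power. Recruitment has closed, and the reported retention of 78% is better than the 71.3% needed even for 107 per group. On this view there is a gap in the explanation and no weakness in the trial.

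Most of this stands. It rules out a flat statement that 300 misses 80% power; a shortfall, to 76%, exists only under the corrected formula. It does not rescue the text, which gives 107 as the requirement and never mentions 97. If the uncorrected figure was the source of 300, the section changed formula between two sentences.

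A reader might also infer that inflating for compliance is the wrong kind of adjustment under intention-to-treat, and that non-completers dilute the effect. If no non-completer benefits and all 150 per arm are analysed, 20 points become 0.65 × 20 = 13 (36% vs 49%), with power of 58% corrected or 63% uncorrected. The documents do not support this as a stated shortfall, for three reasons:
- The programme runs alongside the follow-up visits, so not completing it may largely mean leaving the study, and inflating for that is ordinary.
- The app stays available throughout pregnancy with messages three times a week, so zero benefit in every non-completer is an extreme assumption.
- The Study Hypothesis attaches the 20% to the programme as such, so it may already be the effect among all women offered it.

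Those figures are a worst-case illustration and no part of this point. What remains is that the section does not say which meaning of 65% it uses.

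**Conclusion.** The point holds in limited form. From the stated inputs, 107 per group at 65% requires 330 women; 300 is 30 (9%) fewer and leaves about 97 per group. That is an arithmetic inconsistency within one section, and it does not depend on the meaning given to 65%.

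The consequence for power does depend on the formula: about 76% by the corrected formula that produced 107, about 80% without the correction. Both values assume that 65% of women are analysable in each arm and that the comparison is 36% versus 56% as proportions. They do not describe the power of a comparison of mean minutes of activity, which is how the abstract defines the physical activity outcome.

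Mixing two formulas is the likeliest explanation, since only the uncorrected 97 leads to 300, but the document does not confirm it. The reported 22% loss is within the 28.7% that 300 allows for 107 per group, so the evidence so far does not show an undersized trial. That remains provisional until follow-up is finished.

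**What to change.** Keep 300 and correct the Sample Size Calculation section in one of two ways:

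1. Keep 107 per group, name the continuity-corrected formula, and state that 300 preserves 107 per group only if at least 71.3% are retained (loss up to 28.7%). Add that at 65% it leaves about 97 per group and 76% power by that formula.
2. State that 300 rests on the uncorrected formula, 97 per group at 65% with 80% power, and replace 107 with 97. Recalculate the diet and supplement figure on the same basis (39 in place of 45).

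In either case, say whether 65% means women retained for analysis or women completing the programme, since the analysis is intention-to-treat and the two are handled differently.

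The cost is a few sentences. No extra women are needed, and neither the design nor the analysis changes.
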